### Randomization and Allocation

We will use a block- randomization, stratified in groups for center to assign participants to the high- intensity exercise group, moderate- intensity exercise group and the control group in a 1:1:1 ratio. For the hierarchical random assignment operation, the statistical unit responsible adopted the SAS version 9.2 statistical software (procedure 'PROC PLAN') to complete program writing and randomization operations. The random distribution results will be released through the network of a central random distribution system. The results of random allocation will be managed by a person designated by the research group, and the results will be executed independently by clinicians. Due to the interventional study design, blinding is impossible for patients and clinical operators. However, the examiners, researchers collecting data on outcome indicators, data managers, and statisticians will be blinded.

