### Statistical Methods

The calculation of the sample size will be based on the primary outcome of the RCT. The sample size calculation was performed using PASS V11.0 (NCSS Company of the United States) with the following calculation formula:

$$\begin{array}{l} n=\Psi^{2}\left[\sum_{i=1}^{k}s_{i}^{2}/k\right]/\left[\sum_{i=1}^{k}{\left({\bar{X}}_{i}-\bar{X}\right)}^{2}/\left(k-1\right)\right]\left(k\;=\;3\right) \end{array}$$

The parameters are set to double-sided α = 0.05, β = 0.1, Power = 1–β = 90%, the average difference in peak VO_2_ of the three groups were 0, 2, 4(ml/kg/min) and the average difference in MLHFQ of the three groups were 2, 12, 10. The corresponding standard difference values of peakVO_2_ were 6, 4, 6 (ml/kg/min) and MLHFQ were 5, 18, 16.

The parameter estimation is based on the results of previous researches (22, 42, 43).

A total of 180 cases were required for the three groups, 60 patients in each group, considering the 20% loss to follow-up rate and stratification factors. Because each of the primary endpoints can be individually reflected in clinical significance. Therefore, if one of the two primary endpoints of the intervention group improves significantly, the study is successful.

Blinded statistical analysis will be performed by qualified statisticians using PASW Statistics 18.0 (IBM SPSS Inc., Armonk, New York, USA). The measurement data will be expressed as mean ± standard deviation (x ± s), measurement data by *t* test, and count data by chi-square test. The clinical events of the treatment groups will be statistically compared, according to the principle of intention-to-treat. The Kaplan–Meier method will be used to calculate the cumulative event rate. The event time of all patients will be measured starting from the randomization time (time zero). We will collect all available information on clinical events until the last patient contact, including patients who withdraw consent or those lost to follow-up. Relative risk (RR) will be calculated using the Cox proportional hazard model. If a sufficient number of events occur, the Kaplan–Meier curve will be used for stratified analysis of the exercise group, and the log-rank test will be used to test the difference in survival. The significance level will be set at *p* < 0.05.

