### Trial Management and Quality Control

The management structure includes a trial management team, a data monitoring committee, and a trial steering committee.

The trial management team (including two physicians and three investigators) is responsible for the implementation of the trial and will meet weekly to discuss the progress of the trial. The data monitoring committee is composed of three clinicians and two biostatisticians, and independently evaluates the safety, scientific validity and completeness of clinical trials. The data monitoring committee will convene a meeting before the start of patient recruitment and once a month after the patient begins to intervene. The person in charge of the center monitors the intermediate results during the clinical trial. Once serious side effects occur, the trial should be stopped immediately. If there are significant differences in the efficacy of the three groups (HIT group, MIT group, and control group), the trial will be considered to be terminated. Responsibility of the test steering committee is to approve the main research plans and revisions, supervise the test, guide the test, and solve the problems of the test management team. The committee will be composed of four experts and will meet at least once every 6 months.

Before recruitment, the entire research team needs to participate in a training seminar. The data collected in this trial will include questionnaire information, medical chart review and test results. Professionals double-enter the data and store the data confidentially in the electronic database. The person in charge of the sub-center has the right to access the data set of the sub-center, and the person in charge of the project has the right to access the final data set of all the centers. Researchers and sponsors will inform participants and other relevant personnel of the results of the trial by publishing articles. The data quality will be regularly checked by the research assistant and supervised by the supervisor.

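### Termination for efficacy is tied to unadjusted "If there are significant differences in the efficacy of the three groups", with interim results monitored outside the data monitoring committee, in a trial sized for one final test at 0.05

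*Protocol article*

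**What the plan says.** Three parts of the protocol article bear on this.

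- **Trial Management and Quality Control.** "The person in charge of the center monitors the intermediate results during the clinical trial". Two sentences later comes the efficacy trigger: "If there are significant differences in the efficacy of the three groups", with the three arms named in brackets, ending the trial will be considered. The same section describes a data monitoring committee that works independently. Its remit is safety, scientific validity and completeness. It meets before recruitment and then "once a month after the patient begins to intervene".
- **Statistical Methods.** The sample size rests on "double-sided α = 0.05, β = 0.1, Power = 1–β = 90"%, with 60 patients per group and 180 in all after 20% loss. For the analysis, "The significance level will be set at *p* < 0.05". No other level appears anywhere in the article.
- **Randomization and Allocation.** Patients and clinical operators cannot be blinded, but "the examiners, researchers collecting data on outcome indicators, data managers, and statisticians will be blinded".

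**The concern.** The article does more than leave interim monitoring to a charter or analysis plan. It names a trigger (significant differences), a consequence (possible termination) and a person who watches. A later document would have to correct this text, not merely complete it. Statistical Methods also uses significance to define trial success and gives 0.05 as the only level, so the natural reading of the trigger is an ordinary test at 0.05.

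Three things are at stake:

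- **False-positive risk.** A design with its full 0.05 committed to one final test has none left for an earlier test that can end the trial with a claim of efficacy.
- **Size of the effect.** A trial stopped because an early difference crossed 0.05 tends to report too large a difference.
- **Who knows what.** Peak VO2 depends on effort and MLHFQ is self-reported, in a trial where patients and clinicians know the arm. Arm-level results known at a centre could affect encouragement and testing.

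**Working it through.** **Step 1: is the sample size a fixed design?** The inputs are from Statistical Methods. For peak VO2 the means "of the three groups were 0, 2, 4(ml/kg/min") have SDs 6, 4 and 6. For MLHFQ, "the average difference in MLHFQ of the three groups were 2, 12, 10", with SDs 5, 18 and 16. The stated formula is n = Ψ² × (mean variance) / (between-group sum of squares / (k − 1)), with k = 3.

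- Peak VO2: mean variance (36 + 16 + 36)/3 = 29.33. Sum of squares about the mean of 2 is 4 + 0 + 4 = 8, and 8/2 = 4. So n = 7.33 Ψ². Solved with the noncentral F distribution at two-sided 0.05 and 90% power, n = 48. With 20% loss, 48/0.8 = 60.
- MLHFQ: mean variance (25 + 324 + 256)/3 = 201.67. Sum of squares about the mean of 8 is 36 + 16 + 4 = 56, and 56/2 = 28. So n = 7.20 Ψ², which solves to 47, and 47/0.8 = 58.75, rounded up to 59.

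The stated 60 per group and 180 in total are reproduced with one analysis at the full 0.05. There is no allowance for interim testing.

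**Step 2: what does testing at 0.05 on the way do?** The number of looks is not in the article, so it is assumed. The simulation was under no difference: 40,000 trials, 48 evaluable patients per arm, equally spaced looks including the final one, each tested at 0.05, for one endpoint. Two tests were used: the three-group F test, which matches the sample-size formula, and a single pairwise t test, which matches the test named for measurement data.

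| Looks, final included | F test | One t test | Constant per-look level that restores 0.05 (F test) |
|---|---|---|---|
| 1 | 0.050 | 0.049 | 0.050 |
| 2 | 0.083 | 0.082 | 0.030 |
| 3 | 0.109 | 0.107 | 0.022 |
| 5 | 0.148 | 0.143 | 0.015 |

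The simulation error at 0.083 is about √(0.083 × 0.917/40,000) = 0.0014. A separate simulation of cumulative z statistics with 100,000 replicates gave 0.084, 0.108 and 0.141 for 2, 3 and 5 looks, in close agreement.

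**Step 3: why an early stop overstates the effect.** Take a pairwise comparison of peak VO2 with the average SD, √29.33 = 5.42.

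- Halfway, 24 per arm: the difference must exceed about 2.01 × 5.42 × √(2/24) = 3.1 ml/kg/min to reach p < 0.05.
- At the end, 48 per arm: about 1.99 × 5.42 × √(2/48) = 2.2.

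The planned difference between neighbouring values is 2. A halfway stop on such a comparison would therefore report at least one and a half times that figure.

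**The case against.** The strongest reply is that this is a condensed article. The number of looks, the boundary and the committee's procedures usually sit in an analysis plan or charter that is not shown, and termination is only to be considered. Both points are fair. Their absence is not the finding, and the error rates above apply only if the trigger is acted on at 0.05. The monitoring section does not itself tie the word significant to that level. What remains is that the article states the trigger in those words and offers no other level to read it by.

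A reader might also infer four stronger things that the article does not support.

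- **Monthly efficacy looks.** The monthly meetings are the committee's, and its stated remit does not name efficacy. The primary outcomes are measured at 12 weeks, so the earliest meetings could hold no primary data. The simulated 22% for twelve looks therefore has no basis in the text.
- **Error rates of 42% to 66%.** Such figures arise if all six comparisons (two endpoints, three pairs, assumed correlation 0.3) are tested at 3 to 12 looks. But 22.5% is already there with a single look. That part is a separate multiplicity question.
- **A breach of blinding.** The head of the centre is not among the blinded roles. The article does not say that interim results are shown by arm or passed to blinded staff, and a coded-group analysis would be compatible with it. The risk is real, but no contradiction is stated.
- **A recruiting investigator as monitor.** The article distinguishes centre from sub-centre and mentions a coordination centre, so the role is ambiguous. On either reading it is not the independent committee.

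**Conclusion.** The point holds in this form: the efficacy-termination rule is badly fixed, and responsibility for interim results is placed outside the body set up to be independent. The loss of error control does not need many looks. One interim test at 0.05 that can end the trial with a claim of efficacy takes a nominal 5% to about 8% for one endpoint, three looks take it to 11%, and five to 14–15%.

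These figures assume equally spaced looks, 48 evaluable patients per arm, and stopping whenever p < 0.05. Fewer looks, or restraint in acting on them, would lower them. On blinding, the conclusion is limited to a risk: the article describes no barrier between arm-level interim results and the staff who are meant to stay blinded.

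**What to change.** Preferably, delete the efficacy-termination sentence. If an early look is wanted, replace the sentence with one look at a pre-set amount of 12-week data, carried out by the data monitoring committee, on a named endpoint and comparison, with a Haybittle-Peto boundary of p < 0.001. For that comparison the overall error is then at most 0.001 + 0.05 = 0.051, so the final test can stay essentially at 0.05. No extra patients are needed.

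In the same section, state that only the committee sees results by arm, and that the head of the centre sees pooled data on recruitment, data quality and safety.

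The cost is two sentences in the protocol and matching text in the committee's charter. The trial is already recruiting, so the change should be made before anyone compares outcomes by arm. What is lost is the option to stop early on ordinary significance, which is a small loss for a 12-week endpoint.

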### Trial Organization

Before enrolling patients, the protocol will be approved by the relevant institutional review boards, research ethics boards, and ethics committees of all the participating centers and the coordination center.

The clinical trial will be conducted in accordance with local laws. The study has been approved by Regional Committees for Medical Research Ethics of all participating centers (2020-KYSB-177). The study is registered at http://www.chictr.org.cn/ and the registration number is ChiCTR2000036381. The trial started in December 2020 and is currently recruiting.

## Discussion

The exercise-based CR is recommended in the guidelines for HFrEF but is still in infancy in China, where exercise-based CR services are rare in most regions, and the most suitable intensity ET for HFrEF patients remains unknown. Compared with global HFrEF exercise rehabilitation, HFrEF exercise rehabilitation in China started late and is still developing. Affected by factors, such as Chinese health and medical conditions and patients' exercise preferences, the overall level of CR in HFrEF still has some gaps compared with foreign countries. However, CR is a healthy behavior intervention affected by the social environment, cognition, and humanities. Simply introducing foreign experience cannot solve China's practical problems. The guidelines that are widely accepted abroad are referenced in China, but they need to be used in conjunction with China's actual adjustments. In this case, China currently lacks reference standards and effectiveness data on exercise intensity for HFrEF rehabilitation. The results of multi-center, randomized controlled registration studies from China are urgently needed to provide high-quality evidence and data from China.

To our knowledge, this is the first multicenter randomized controlled trial protocol to explore the appropriate exercise intensity for patients with HFrEF in China. The HF-EI trial will assess the impact of aerobic exercise intensity on the peak VO_2_ and QoL in patients with HFrEF. It also provides a rationale for improving functional capacity and cardiovascular prognosis in patients with HFrEF. We hope that this research fills the gap in the literature and offers high-quality evidence on the recommendations for the treatment of HFrEF.

AT relates to the point when the exercise load increases to a certain amount and the tissue demand for oxygen exceeds the amount that the circulation can provide, and the tissues undergo anaerobic metabolism to provide more energy. The critical point from aerobic metabolism to anaerobic metabolism is called AT, expressed as the threshold oxygen consumption of anaerobic metabolism (VO_2_ AT), equivalent to 50–60% of peak oxygen consumption, and directly detected by CPET (44). The advantages of using AT as the basis for formulating exercise prescriptions are sub-maximal exercise intensity, which can prevent the continuous increase of lactic acid levels, avoid hyperventilation and shortness of breath, avoid metabolic alkalosis, reduce the occurrence of overload on the heart and arrhythmia, and ensure high safety. Aerobic exercise with the intensity of the AT has protective effects on CHF, confirmed by the literature (45). For patients with HFrEF, exercise intensity is a range, not a point; AT belongs to sub-maximum medium intensity. Although 70% of peakVO_2_ is high- intensity, it is not ultra-high intensity. This study will explore the effects of these two different intensities.

AT intensity has not been widely accepted internationally. This study compares the effectiveness and safety of AT intensity and high intensity in patients with HF, and aims to reflect the superiority of AT intensity exercise. It has reference value for other colleagues in the world.

Limitations of the study should be recognized as follows: lost to follow-up, influencing factors including patient age, difficulties attending appointments, concurrent illnesses, and the nature of the intervention that made blinding impossible. We made every effort to ensure that evaluators, laboratory technicians and statisticians remain unaware of the treatment allocation.

Altogether, the results of the HF-EI trial may provide evidence on the effective delivery of a contextually adapted exercise-based CR program in China. At the same time, it provides evidence of AT exercise intensity for the world's CR field.

## Conclusions

The HF-EI trial will assess the effects of different aerobic exercise intensities on peak VO_2_ and QoL in patients with HFrEF. It will provide a rationale for improving functional capacity and cardiovascular outcomes in patients with HFrEF.

## Ethics Statement

The studies involving human participants were reviewed and approved by Shanghai Tongji Hospital Ethics Committee. The patients/participants provided their written informed consent to participate in this study.

## Abbreviations

6MWD: 6-min walk distance
6MWT: 6-min walking test
AT: anaerobic threshold
BMI: body mass index
CHF: chronic heart failure
CHS: China hypertension survey
CPET: cardiopulmonary exercise testing
CR: cardiac rehabilitation
ECG: electrocardiogram
eGFR: estimated glomerular filtration rate
ESC: European Society of Cardiology
ET: Exercise training
ExTraMATCH: Exercise Training Meta-Analysis of Trials in Chronic Heart Failure
GAD-7: General Anxiety Disorder-7
HF: heart failure
HF-EI trial: the efficacy and safety of different aerobic exercise intensities in patients with heart failure with reduced ejection fraction
HFrEF: heart failure with reduced ejection fraction
HIT: high intensity training
ICD: implantable cardioverter-defibrillator
LVEF: left ventricle ejection fraction
MET: metabolic equivalent
MIT: moderate intensity training
MLHFQ: Minnesota Living with Heart Failure Questionnaire scores
NT pro-BNP: N-terminal prohormone of brain natriuretic peptide
NYHA: New York Heart Association
Peak VO_2_: peak oxygen consumption
PHQ-9: the Patient Health Questionnaire-9
QoL: quality of life
RCT: randomized controlled trial
RR: relative risk
SPIRIT: Standard Protocol Items: Recommendations for Interventional Trials.
